## Abstract

**Introduction:**

The incidence of chronic hepatitis B (CHB) combined with metabolism-associated fatty liver disease (MAFLD) is increasing annually, and the presence of MAFLD may influence the clinical assessment of viral activity and transaminase levels. However, it remains unclear whether MAFLD impacts the achievement of clinical cure in CHB patients treated with polyethylene glycol interferon (Peg-IFN).

**Methods:**

A prospective cohort study was conducted to enroll patients with dominant CHB (on NA treatment, HBsAg <1,500 IU/mL, HBeAg negative, HBV DNA <10 IU/mL) and patients with dominant CHB combined with MAFLD, all of whom were treated with Peg-IFN. The study aimed to assess the efficacy and safety of Peg-IFN treatment and to elucidate the effect of MAFLD on achieving HBsAg clearance in these patients. Additionally, the study explored the T-lymphocyte characteristics of patients with CHB combined with MAFLD, analyzed the role of T-lymphocytes expressing inhibitory receptors in HBsAg clearance, and investigated the immunological mechanisms of HBsAg clearance through single-cell transcriptome sequencing technology.

**Ethics and dissemination:**

Patients will be recruited at four medical centers in Beijing and Hebei, and written informed consent will be obtained to inform participants of the purpose of the study, potential risks, and benefits. Ethical approval has been granted for the study, which will focus on 48-week HBsAg clearance, and a detailed follow-up and adverse event monitoring plan has been developed.

**Strengths and limitations of this study:**

Strengths are that this study fills the gap in treatment strategies for patients with CHB combined with MAFLD and provides important treatment guidance to clinicians; the multicenter design may increase the diversity of the sample size, reduce the bias of single-center studies, and improve the external validity of the results. Limitations are that interferon therapy is often associated with side effects, which may lead to lower patient adherence and affect long-term follow-up and outcome monitoring of the study; the heterogeneity of the MAFLD population may have different effects on the efficacy of interferon therapy.

**Clinical trial registration:**

http://www.chictr.org.cn/bin/project/edit?pid=231498, identifier ChiCTR2400084913.

## Introduction

### Background and rationale

In 2016, the World Health Organization (WHO) proposed “eliminating viral hepatitis as a major public health threat by 2030” (1). In recent years, the incidence of HBV infection has shown a significant downward trend; however, due to its large patient population, China continues to bear the highest disease burden of HBV infection globally, with 74 million affected individuals (2). This reality indicates that China remains far from meeting the WHO’s target, making the task of elimination particularly challenging.

Previous studies have concluded that HBV DNA seroclearance significantly reduces the risk of hepatocellular carcinoma (HCC) (3). However, these patients may still face the risk of reactivation. Among those with undetectable viral loads, patients with low serum HBsAg levels (<1,000 IU/mL) have the lowest risk of HCC (4). Thus, further HBsAg seroclearance is considered the best marker of HBV immune clearance. The 2022 Chinese Guidelines for the Prevention and Control of Chronic Hepatitis B emphasize that “for some patients with suitable conditions, a cure for hepatitis B should be pursued.” The guidelines further state that patients with undetectable HBV DNA, HBeAg conversion, and HBsAg <1,500 IU/mL after nucleotide analog (NA) treatment represent an advantageous population for achieving HBsAg clearance. These patients may be considered for additional treatment with polyethylene glycol interferon (Peg-IFN) in pursuit of a clinical cure (5).

In addition, non-alcoholic fatty liver disease (NAFLD) has become the most prevalent chronic liver disease in both China and globally. The most recent data report the global prevalence of NAFLD to be 30% and rising (6, 7). In 2020, the International Fatty Liver Nomenclature Panel redefined fatty liver in individuals with overweight/obesity, type 2 diabetes mellitus, or multiple metabolic disorders as metabolism-associated fatty liver disease (MAFLD) (8). In 2023, the European Annual Congress of Liver Diseases, along with the Liver Disease Associations of the United States, Europe, and Latin America, proposed that the alternative term for NAFLD should be metabolic dysfunction-associated steatohepatopathy (MASLD) (9). The prevalence of MAFLD in China was about 17.6% in 2016, with an estimated 246 million individuals affected, and is projected to rise to 29.1% by 2030, reaching 315 million cases, making MAFLD the most common chronic liver disease (10). The international expert consensus on metabolism-associated fatty liver disease notes that, with the dramatic global increase in MAFLD prevalence, it often coexists with other liver diseases, such as viral hepatitis. Large North American cohort studies have shown the prevalence of CHB combined with MAFLD to be 31.4% (11), while a single-center retrospective study in the Netherlands reported an increase from 17.2 to 24.3% in such patients (12). A recent meta-analysis of 53 studies found the prevalence of MAFLD in patients with CHB to be 32.83% (13).

Whether MAFLD affects the antiviral efficacy of hepatitis B treatments, including HBV DNA suppression, HBeAg conversion, and HBsAg clearance, remains controversial. Most current studies focus on NA treatment, with goals primarily related to HBV DNA suppression and HBeAg conversion. However, research on HBsAg clearance, an indicator of clinical cure, is limited. Notably, the impact of MAFLD on achieving clinical cure in the Peg-IFN treatment-advantaged CHB population has not yet been reported and is in urgent need of investigation. Some studies suggest that the presence of MAFLD could potentially hinder the response to interferon therapy, possibly due to alterations in immune function or liver metabolism (14). However, the findings are inconsistent, with certain studies indicating no significant impact of MAFLD on Peg-IFN efficacy (15), while others suggest that MAFLD may contribute to reduced treatment efficacy or slower rates of HBsAg clearance (16).

These conflicting results highlight a major gap in the current understanding of how MAFLD affects Peg-IFN therapy outcomes, particularly regarding HBsAg clearance, and underscore the need for further investigation. Our study aims to address this gap by evaluating the impact of MAFLD on the response to Peg-IFN treatment in chronic hepatitis B patients, specifically focusing on the achievement of HBsAg clearance as a marker of clinical cure. Additionally, the impact of hepatic steatosis on the immune status of CHB patients, such as T-lymphocyte function, has not been previously reported, and it remains unclear whether MAFLD affects clinical cure by influencing the immune status of the body.

### Objectives

In this study, a prospective clinical cohort of Peg-IFN-treated patients with advantageous CHB combined with MAFLD was established to verify the efficacy and safety of Peg-IFN in achieving HBsAg clearance. The study aims to elucidate the impact of MAFLD on HBsAg clearance in these patients and to provide practical guidance for clinicians in accurately screening suitable candidates and adjusting treatment regimens as needed. Flow cytometry was used to examine the number and function of peripheral blood T-lymphocytes expressing inhibitory receptors in both HBsAg-cleared and non-cleared patients at baseline and various time points during treatment. This was done to explore the characteristics of T-lymphocytes in CHB combined with MAFLD and to clarify the role of inhibitory receptor-expressing T-lymphocytes in HBsAg clearance. Additionally, single-cell transcriptome sequencing technology was applied to analyze changes in the gene expression profiles of immune cells in CHB patients with MAFLD treated with Peg-IFN, aiming to trace the genetic information profile changes in immune cells during HBsAg clearance and to explore the genetic-immunological mechanisms underlying HBsAg clearance.

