### Trial design

This prospective study investigates the impact of MAFLD on HBsAg clearance in CHB patients treated with PEG-IFN (135ug/180ug/week for 48 weeks). Patients are divided into two groups: CHB patients (*n* = 100) and CHB with MAFLD patients (*n* = 100). After treatment, participants are categorized into HBsAg clearance responders and non-responders. For HBsAg responders and HBsAg non-responders, analyzes differences in HBsAg clearance rates between CHB and CHB with MAFLD patients. Explores the impact of MAFLD on HBsAg clearance mechanisms using IHC and other methods. Compares the immunosuppressive microenvironment between responders and non-responders, focusing on T-cell characteristics. Identifies immune mechanisms contributing to HBsAg clearance. The flow chart of this study is shown in Figure 1.

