T lymphocytes play a crucial role in the progression of HBV disease, including viral clearance, the development of hepatitis, cirrhosis, and hepatocellular carcinoma, as well as in response to antiviral therapy. CD8+ T cells are particularly important, as they can induce apoptosis in virus-infected hepatocytes. Additionally, they inhibit HBV gene expression and replication in hepatocytes through a non-cytolytic mechanism by secreting IFN-*γ*. This dual function of CD8+ T cells—mediating apoptosis and inhibiting viral replication—highlights their essential role in controlling HBV infection. When HBV infection becomes chronic, T cells gradually become dysfunctional and lose their immune efficacy as the infection progresses and antigen exposure continues. This dysfunction is characterized by a decrease in the secretion of cytotoxic factors, such as IL-2, IFN-γ, and TNF (26, 27), and an increase in the secretion of immunosuppressive factors like IL-10 and transforming growth factor-beta (TGF-*β*). Additionally, there is increased expression of inhibitory receptors such as programmed death protein 1 (PD-1), cytotoxic T-lymphocyte-associated antigen-4 (CTLA-4), and T-cell immunoglobulin and mucin structural domain-3 (Tim-3) (28, 29). Inhibitory receptors are likely the primary reason for the loss of T-lymphocyte function, leading to the body’s inability to effectively clear HBV (30). A therapeutic strategy that rescues functionally exhausted T cells by blocking inhibitory receptor signaling pathways, thereby enhancing the immune response, could integrate immunotherapy with antiviral therapy. This approach holds promise as a reliable option for patients with chronic HBV infection to achieve a functional cure.

Recent studies have reported that hepatic CD8+ T cells in MAFLD mice may play a role in alleviating hepatic inflammation and fibrosis (31). Additionally, the number of peripheral blood Th1 cells in patients with MAFLD is significantly higher than in healthy individuals, leading to the hypothesis that Th1 cells may have a pro-inflammatory role (32). However, the state of T-lymphocyte immunocompetence in patients with CHB combined with MAFLD has not yet been reported.

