Sequencing of immune cells, such as T lymphocytes and DC cells, from liver cancer patients has revealed the characteristics of immune cells within the liver cancer environment, aiding in the development of more effective immunotherapeutic targets (33). However, the application of single-cell sequencing technology in populations with CHB combined with MAFLD has not yet been explored, particularly in investigating the mechanisms involved in HBsAg clearance. In this study, we aim to use transcriptome single-cell sequencing to explore the immunomolecular mechanisms of HBsAg clearance in CHB patients with MAFLD who are receiving Peg-IFN treatment. This approach will provide a multi-stage, dynamic, and high-resolution immune landscape of the HBsAg clearance process, clarify the gene regulation of immune cells during HBsAg clearance, uncover the immune cytogenetic basis of this clearance, and identify the molecular immunogenetic markers that determine successful HBsAg clearance. In addition, although this study has adopted a prospective and multicenter study protocol to reduce sampling and follow-up bias, there are still some limitations: (1) Given that the study is multicenter and cohort-based, there may be variability in treatment outcomes due to differences in patient populations, hospital settings, and clinician practices. While we aim to include a representative sample, the findings may not be generalizable to all HBV patients, particularly those outside of the study centers or those with more advanced liver disease. (2) The study relies on patient adherence to treatment protocols, including Peg-IFN therapy, and the potential for non-compliance or early dropout could impact the results, particularly the achievement of HBsAg clearance. (3) While we will attempt to control for common confounding factors such as age, gender, and baseline liver function, there may be other unmeasured factors (e.g., genetic predispositions, lifestyle habits, or co-infections) that could influence the treatment response and the success of Peg-IFN therapy.

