## Experimental state

The study has received all approvals from the Ethics Committee to start in all participating hospitals. The study was registered on May 28, 2024 (ChiCTR2400084913). Patient enrollment started on June 1, 2024.

Timeline and Milestones:

By December 2024:

(1) Develop and finalize various SOPs.(2) Enroll eligible CHB patients.(3) Peg-IFN combined with NA therapy should be administered to both the dominant CHB population and the CHB combined with MAFLD patients.(4) Conduct regular follow-ups to monitor patient progress.

January 2025 to December 2025:

Complete the enrollment of all patients.

January 2026 to December 2026:

(1) Analyze and compare the number and function of inhibitory receptor T-lymphocytes between the two groups.(2) Assess differences in HBsAg clearance rates.(3) Compare the number and function of inhibitory receptor T-lymphocytes between HBsAg-cleared and non-cleared patients.(4) Use single-cell sequencing technology to analyze the mechanisms underlying HBsAg clearance.

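### On-treatment T-cell comparisons between cleared and non-cleared patients do not separate samples taken before HBsAg loss from those after it, so a consequence of clearance could be read as a contributor to it

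*Protocol article*

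**What the plan says.** The protocol article's Trial design section fixes the groups by outcome: "After treatment, participants are categorized into HBsAg clearance responders and non-responders". The Objectives section then compares peripheral-blood T cells "in both HBsAg-cleared and non-cleared patients at baseline and various time points during treatment", with the purpose "to clarify the role of inhibitory receptor-expressing T-lymphocytes in HBsAg clearance". The Discussion repeats the comparison at baseline and during treatment. The Experimental state section schedules it for 2026: "Compare the number and function of inhibitory receptor T-lymphocytes between HBsAg-cleared and non-cleared patients". Trial design words the aim causally: "Identifies immune mechanisms contributing to HBsAg clearance".

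On the biology, the Discussion states that in chronic infection "T cells gradually become dysfunctional and lose their immune efficacy as the infection progresses and antigen exposure continues", with raised expression of PD-1, CTLA-4 and Tim-3.

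Single-cell sequencing is described differently. The Objectives section says it is used "aiming to trace the genetic information profile changes in immune cells during HBsAg clearance", and the Discussion hopes to "identify the molecular immunogenetic markers that determine successful HBsAg clearance".

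Methods for any additional analyses plans mixed-effects models for repeated immune measurements. It also plans a Cox model relating immune markers to outcomes such as sustained seroclearance.

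**The concern.** The group label comes from the end of follow-up, while the samples come from fixed visits. Once a patient has cleared, each later sample reflects a body without circulating HBsAg. A non-cleared patient's sample at the same visit reflects continuing exposure. If exposure affects T-cell state, as the Discussion says, the two groups can differ at weeks 24, 36 or 48 even when T cells played no part in clearance.

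A visit-by-visit contrast cannot tell a cause from a consequence. What is at stake is the mechanistic objective: the role of inhibitory-receptor T cells and the therapeutic targets that the Discussion hopes to draw from it.

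**Working it through.** The plan gives no figure on this point, so the check is of timing and of what the stated methods can separate.

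**Inputs from the article**
- Visits at baseline and weeks 12, 24, 36 and 48, with HBsAg quantified and blood taken for immunology (Additional consent provisions).
- All patients HBsAg positive at entry (Eligibility criteria).
- Clearance of 35% in CHB and 60% in CHB with MAFLD, 100 patients per group (Sample size). These rates give the stated 79 per group under the unpooled two-sided formula: (0.35×0.65 + 0.60×0.40)×(1.960+1.282)²/0.25² = 78.6, rounded up to 79. Expected clearers: 35 + 60 = 95 of 200.

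**Inputs that are assumed.** The article does not say when clearance occurs. Three patterns for the first HBsAg-negative visit (weeks 12/24/36/48) are used: early 40/30/20/10%, uniform 25% each, late 10/20/30/40%.

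**Step 1: share of clearers' on-treatment samples at or after clearance.** A patient first negative at week 12, 24, 36 or 48 contributes 4, 3, 2 or 1 such samples out of 4.
- Early: (4×0.40 + 3×0.30 + 2×0.20 + 1×0.10)/4 = 3.0/4 = 75%.
- Uniform: (4+3+2+1)×0.25/4 = 2.5/4 = 62.5%.
- Late: (4×0.10 + 3×0.20 + 2×0.30 + 1×0.40)/4 = 2.0/4 = 50%.
- At week 48 it is 100% under every pattern, barring reversion. At baseline it is 0%.

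**Step 2: does the plan expect early clearance?** Intervention description lets treatment stop before week 48 once seroconversion has held for 24 weeks. That requires seroconversion before week 48 − 24 = 24, so some patients are expected to have several post-clearance samples. Those who stop early would also differ in drug exposure at late visits.

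**Step 3: can this produce a false signal?** Simulation with 2,000 runs per setting, 95 cleared and 105 non-cleared patients, and within-patient correlation 0.5. The marker has no effect on clearance but shifts by 0.3, 0.5 or 0.8 SD once clearance has occurred (assumed sizes). Share of runs with p < 0.05 when each patient's mean of the four on-treatment samples is compared between groups:

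| Timing | 0.3 SD | 0.5 SD | 0.8 SD |
|---|---|---|---|
| Early | 52% | 91% | 100% |
| Uniform | 37% | 79% | 99% |
| Late | 27% | 58% | 94% |

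Using only pre-clearance samples (baseline, or week 12 in patients not yet cleared), rejection was about 4% to 6% in every setting.

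**Step 4: do the planned models prevent it?** The mixed-effects models handle correlation within a patient, not the order of marker and event. The Cox model could respect that order, but the article does not say whether markers are baseline or time-updated. It also lists HBsAg clearance among the markers while sustained seroclearance is an outcome.

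**The case against.** The strongest reply is that this is an exploratory analysis in a condensed article. Baseline is already a named comparison point, HBsAg is measured at every visit, and a Cox model is planned, so an analysis plan that is not shown may make the separation. The Discussion also describes T-cell dysfunction as gradual. It does not say that receptor expression falls within weeks of antigen loss.

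Much of this stands. The baseline comparison is sound, the data allow the separation, and the effect is possible rather than certain. It does not dispose of the point, because the article itself states the grouping, the on-treatment sampling times and the causal aim, and the methods it names do not enforce temporal order.

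The size is also open to challenge. A share of samples is not a measure of bias. The rejection rates depend on shifts that the article does not supply and on averaging the four visits, which it does not prescribe. The figure of 95 clearers ignores the 15% dropout (0.85 × 95 is about 81).

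Three stronger readings are tempting but unsupported. A reader might infer that single-cell profiles are also contrasted between cleared and non-cleared patients, but no section states that; the sequencing traces changes during clearance, and only the aim of finding markers that determine it carries a similar risk. A reader might infer that the promised guidance on selecting patients is undermined, but the Objectives section ties that guidance to the effect of MAFLD, not to T-cell markers. And a reader might infer that a consequence will be reported as a cause; the text supports only that it could be.

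**Conclusion.** The point holds for the flow-cytometry T-cell comparison at on-treatment visits. As written, the comparison cannot distinguish a contributor to clearance from a result of it, and the article's own account of antigen exposure makes the second explanation plausible.

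Half to three quarters of clearers' on-treatment samples are affected under the assumed timings, and all of them at week 48 barring reversion. These shares rest on the assumed timing alone. The simulated rejection rates of 27% to 100% rest also on the assumed post-clearance shift, and show that the problem can matter, not how large it will be. The baseline comparison is unaffected, as are the primary and secondary outcomes, none of which is an immune-marker outcome.

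**What to change.** State the following before the immune analysis scheduled for 2026, so that the sampling window is not chosen after results are seen:

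- Base claims about the role or prediction of clearance on baseline samples and on samples taken while the patient is still HBsAg positive. One way is a landmark comparison at each visit among patients still positive then, setting those who clear later against those who do not; week 48 cannot contribute. The other is the planned Cox model with T-cell markers at baseline, or time-updated and lagged to a visit before clearance, and with HBsAg clearance removed from the marker list.
- Report samples at or after clearance separately, as descriptive.
- Present any analysis adjusted for concurrent HBsAg level only as a sensitivity analysis. HBsAg level may lie on the causal path, so adjustment could remove a real T-cell effect. Without adjustment, antigen that is already falling before clearance may still influence the markers, and the report should say so.
- For single-cell sequencing, limit any claim about markers that determine clearance to pre-clearance samples.

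No new visits or blood are needed, because HBsAg results and stored cells exist for each visit. The cost is precision. Of 95 × 4 = 380 on-treatment samples from clearers (no dropout), about 95, 143 or 190 remain under early, uniform or late timing.

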### Trial design

This prospective study investigates the impact of MAFLD on HBsAg clearance in CHB patients treated with PEG-IFN (135ug/180ug/week for 48 weeks). Patients are divided into two groups: CHB patients (*n* = 100) and CHB with MAFLD patients (*n* = 100). After treatment, participants are categorized into HBsAg clearance responders and non-responders. For HBsAg responders and HBsAg non-responders, analyzes differences in HBsAg clearance rates between CHB and CHB with MAFLD patients. Explores the impact of MAFLD on HBsAg clearance mechanisms using IHC and other methods. Compares the immunosuppressive microenvironment between responders and non-responders, focusing on T-cell characteristics. Identifies immune mechanisms contributing to HBsAg clearance. The flow chart of this study is shown in Figure 1.

